## **1.1 TITLE**

Pharmacokinetic study of single administration of rikkunshito (TJ-43) in healthy volunteers

## **1.2 STUDY OBJECTIVE**

To evaluate the pharmacokinetics and safety of Tsumura Rikkunshito Extract Granules (for prescription, hereinafter referred to as “TJ-43”) after single oral doses of 7.5 g (1 sachet 2.5 g × 3 sachets), 5.0 g (1 sachet 2.5 g × 2 sachets), and 2.5 g (1 sachet 2.5 g × 1 sachet) in healthy volunteers

## **1.3 ENDPOINTS**

Pharmacokinetics and safety assessment

## **STUDY POPULATION**

### 1.4.1 Subjects

Healthy volunteers who satisfy all inclusion criteria and do not meet the exclusion criteria

### 1.4.2 Target Sample Size

21 subjects

### 1.4.3 Inclusion Criteria

1) Japanese subjects

2) Subjects aged 20–44 years, inclusive (at the time of informed consent)

3) Subjects with a body mass index (BMI) of 18.5–25 kg/m2

4) Both genders

5) Subjects willing and able to provide written and signed informed consent

### 1.4.4 Exclusion Criteria

1) Subjects with a history of allergic reactions to drugs and food(s)

2) Female subjects who are pregnant, breastfeeding, or planning to become pregnant

3) Subjects who have participated in another clinical study within the past 16 weeks

4) Subjects who have had their blood drawn or who have donated >400 mL of blood within 12 weeks of study drug administration

5) Subjects with a history of a significant hepatic, cardiovascular, or hematological disease

6) Subjects who are under treatment for a disease

7) Subjects who are not able to stop smoking or drinking from 3 days prior to study drug administration until completion of each treatment phase of the study

8) Subjects who are not able to stop using medications (e.g., general cold, anti-allergy, anti-fungal, and Kampo medications) from 7 days prior to study drug administration until completion of each treatment phase of the study

Subjects who consumed supplements* containing Atractylodes Lancea Rhizome, Ginseng, Pinellia Tuber, Poria Sclerotium, Jujube, citrus fruits (Citrus Unshiu Peel), Glycyrrhiza, ginger, and vitamin P within 3 days prior to study drug administration

10) Subjects who used other agents from 7 days prior to study drug administration until completion of each treatment phase of the study

11) Subjects with abnormal clinical laboratory values in screening tests or pre-administration tests that were considered inappropriate for the study by the principal investigator/subinvestigator

12) Subjects who are deemed ineligible for other reasons by the principal investigator/subinvestigator

13) Subjects who test positive for HCV antibody, HBs antigen, or HIV antibody

* Supplements are products that contain any of vitamins, minerals, herbs, and amino acids and aim to supplement a regular diet.

## **1.5 STUDY DESIGN**

Randomized crossover study

## **1.6 DOSAGE AND ADMINISTRATION**

Single oral administration of TJ-43 (for prescription) at doses of 7.5 g (1 sachet 2.5 g × 3 sachets), 5.0 g (1 sachet 2.5 g × 2 sachets), and 2.5 g (1 sachet 2.5 g × 1 sachet)

## **1.7 SCHEDULE OF TIME AND EVENTS**

Subjects will be randomly assigned to Groups A–C after enrollment, and 3 different dosages will be administered to the same subject at 3 separate times. The 3 dosage periods will be designated as phase I, phase II, and phase III, with a washout period of greater than 4 weeks between each treatment period, i.e., between phases I and II and between phases II and III (Table 1).

Table 1 Dosing Schedule

|  | Phase I | Washout period | Phase II | Washout period | Phase III |
| --- | --- | --- | --- | --- | --- |
| Group A | 7.5 g | >4 weeks | 2.5 g | >4 weeks | 5.0 g |
| Group B | 2.5 g | >4 weeks | 5.0 g | >4 weeks | 7.5 g |
| Group C | 5.0 g | >4 weeks | 7.5 g | >4 weeks | - 1. g |

## **1.8 OTHER FACTORS FOR CONTROL**

1) Foods and drinks containing caffeine, alcohol, citrus fruits (grapefruit, orange, tangerine, etc.), vitamin P, ginseng, ginger, Glycyrrhiza (listed on a food label), and garlic (including spices) (see attached references) are prohibited from 3 days prior to study drug administration until completion of each treatment phase of the study. Supplements containing constituents of rikkunshito (Atractylodes Lancea Rhizome, Ginseng, Pinellia Tuber, Poria Sclerotium, Jujube, Citrus Unshiu Peel, Glycyrrhiza, Ginger), processed ginger, and vitamin P are also prohibited. However, foods and drinks that do not contain the above (see attached references) may be consumed at any time. Subjects must have fasted from 20:00 on the eve of study drug administration until 4 h post-dose.

2) Smoking: Smoking is prohibited from 3 days prior to study drug administration until completion of each treatment phase of the study.

3) Use of other medications: Use of other medications is prohibited from 7 days prior to study drug administration until completion of each treatment phase of the study.

## **1.9 STUDY PERIOD**

September 2013–May 2014

# 2 BACKGROUND

Rikkunshito, a traditional medicine described in the classic literature of Kampo [Manbyokaishun], is composed of 8 crude drugs: Atractylodes Lancea Rhizome, Ginseng, Pinellia Tuber, Poria Sclerotium, Jujube, Citrus Unshiu Peel, Glycyrrhiza, Ginger. Rikkunshito is a combination of shikunshito (Atractylodes Lancea Rhizome or Atractylodes Rhizome, Poria Sclerotium, Ginseng, Jujube, Ginger, and Glycyrrhiza) and nichinto (Pinellia Tuber, Citrus Unshiu Peel, Poria Sclerotium, Ginger, and Glycyrrhiza).

Rikkunshito has been widely used for the treatment of “poor digestion, poor appetite, dull feeling in the stomach, fatigue, and cold feet and hands due to anemia.” TJ-43 is a convenient granule form of rikkunshito, which is manufactured by Tsumura with its proprietary dry granulation method and officially approved as a Kampo extract formulation for prescription under the provisions stipulated in “Report No. 120 of the Central Pharmaceutical Affairs Council, Ministry of Health and Welfare, dated May 31, 1985.” TJ-43 has broad clinical applications for the treatment of various digestive symptoms, including gastritis, stomach ache, dull feeling in the stomach, abdominal fullness, loss of appetite, and heartburn1)-3). In recent years, it has been reported that TJ-43 is effective for improving digestive symptoms in patients with gastroesophageal reflux disease4)-5) and functional dyspepsia2),6). Evidence suggests that TJ-43 improves the above-mentioned digestive conditions through functions such as gastric adaptive relaxation6),7), promotion of gastric emptying8)-10), improvement of esophagus clearance5), and regulation of ghrelin secretion and response11)-15). Furthermore, several studies have focused on the active ingredients of TJ-43. It has been reported that atractylodin in Atractylodes Lancea Rhizome promotes ghrelin receptor activity15); pachymic acid in Poria Sclerotium suppresses metabolism of the active form of ghrelin16); and heptamethoxyflavone, nobiletin, and naringenin in Citrus Unshiu Peel as well as liquiritigenin and isoliquiritigenin in Glycyrrhiza promote ghrelin secretion11). While there are several reports on the pharmacological effects of TJ-43, pharmacokinetic studies of the Kampo formulation TJ-43 are limited because of the difficulty in conducting such studies on account of the multiple constituents involved. Although pharmacokinetic studies of isolated constituents such as Glycyrrhiza are occasionally found in literature17),18), no appropriate pharmacokinetic profiling of orally administered constituent crude drug has been conducted clinically.

Therefore, as a prelude to the clinical pharmacokinetic study of TJ-43, we performed a study “Exploratory Pharmacokinetic Study of Rikkunshito (TJ-43) in Healthy Volunteers” to identify the constituents absorbed after administration of TJ-43 in humans in April 201219). As a result, presence of the active constituents of TJ-43, such as atractylodin, a constituent of Atractylodes Lancea Rhizome; pachymic acid, a constituent of Poria Sclerotium; and heptamethoxyflavone, a constituent of Citrus Unshiu Peel, was confirmed in plasma.

Considering the background and results described above, a quantitative clinical pharmacokinetic study on atractylodin, pachymic acid, heptamethoxyflavone, liquiritigenin, isoliquiritigenin, nobiletin, and naringenin was planned to elucidate the pharmacokinetics of each constituent after administration of TJ-43. Long-term use of large amounts of Glycyrrhiza, an ingredient of TJ-43, may cause pseudoaldosteronism. The causal constituents are believed to be glycyrrhetinic acid and glycyrrhetinic acid monoglucuronide, which are metabolites of glycyrrhizin, a constituent of Glycyrrhiza18). To confirm the presence of the constituents of Glycyrrhiza, glycyrrhetinic acid was also analyzed. A quantitative clinical pharmacokinetic study of yokukansan, which contains Glycyrrhiza as an ingredient, showed extremely low levels of glycyrrhetinic acid monoglucuronide20). Therefore, glycyrrhetinic acid monoglucuronide was excluded from analysis in this study. The findings of this study are expected to provide important data regarding adverse drug reactions (ADRs).

We believe that a quantitative pharmacokinetic study of TJ-43 in humans would be extremely useful for understanding the relationship between the basic pharmacological action and constituents of TJ-43. Furthermore, it is important to predict the possibility of accumulation of unchanged compounds or metabolites by evaluating drug clearance.

The present study will be conducted in accordance with the trial protocol and standards specified under the Ministry of Health, Labour and Welfare (MHLW) ordinance regarding Good Clinical Practice (GCP), MHLW ordinance regarding Good Post-Marketing Surveillance/Study Practice (GPSP), and Article 14, Paragraph 3, and Article 80, Paragraph 2, of the Pharmaceutical Affairs Law.

# 3 STUDY OBJECTIVE

## **3.1 STUDY OBJECTIVE**

To evaluate the pharmacokinetics and safety of TJ-43 after single oral doses of 7.5 g (1 sachet 2.5 g × 3 sachets), 5.0 g (1 sachet 2.5 g × 2 sachets), and 2.5 g (1 sachet 2.5 g × 1 sachet) in healthy volunteers.

**3.2 TYPE OF STUDY**

Quantitative study (post-marketing clinical study)

# 4 STUDY POPULATION

**4.1** **SUBJECTS**

# Healthy volunteers who satisfy all inclusion criteria and do not meet the exclusion criteria. A healthy volunteer is a person who does not have a chronic disease and who is able to lead his/her daily life without difficulty.

**4.2 TARGET SAMPLE SIZE**

21 completed subjects

[Rationale for Sample Size Determination]

The conventional sample size required to evaluate pharmacokinetics is 15 subjects. The sample size for this study was set to 21 subjects considering withdrawal, etc. For the definition of the term “completed,” refer to 5.3.1.

**4.3 INCLUSION CRITERIA**

1) Japanese subjects

2) Subjects aged 20–44 years, inclusive (at the time of informed consent)

3) Subjects with a BMI of 18.5–25 kg/m2

4) Both genders

5) Subjects willing and able to provide written and signed informed consent

[Rationale for Inclusion Criteria]

The subjects of this study are Japanese. The purpose of setting the lower age limit is to select adults with the ability to make an informed decision about study participation, whereas the upper age limit serves to dampen the physiological effects of aging from older subjects. BMI within the normal range as specified by the Japan Society for the Study of Obesity is included to minimize the effects of obesity on the distribution of the study drug.

**4.4 EXCLUSION CRITERIA**

1) Subjects with a history of allergic reactions to drugs and food(s)

2) Female subjects who are pregnant, breastfeeding, or planning to become pregnant

3) Subjects who have participated in another clinical study within the past 16 weeks

4) Subjects who have had their blood drawn or who have donated >400 mL of blood within 12 weeks of study drug administration

5) Subjects with a history of a significant hepatic, cardiovascular, or hematological disease

6) Subjects who are under treatment for a disease

7) Subjects who are not able to stop smoking or drinking from 3 days prior to study drug administration until completion of each treatment phase of the study

8) Subjects who are not able to stop taking medications (e.g., general cold, anti-allergy, anti-fungal, and Kampo medications) from 7 days prior to study drug administration until completion of each treatment phase of the study

9) Subjects who consumed supplements* containing Atractylodes Lancea Rhizome, Ginseng, Pinellia Tuber, Poria Sclerotium, Jujube, citrus fruits (Citrus Unshiu Peel), Glycyrrhiza, ginger, and vitamin P within 3 days prior to study drug administration

10) Subjects who used other agents from 7 days prior to study drug administration until completion of each treatment phase of the study

11) Subjects with abnormal clinical laboratory values in screening tests or pre-administration tests that were considered inappropriate for the study by the principal investigator/subinvestigator

12) Subjects who are deemed ineligible for other reasons by the principal investigator/subinvestigator

13) Subjects who test positive for HCV antibody, HBs antigen, or HIV antibody

* Supplements are products that contain any of vitamins, minerals, herbs, and amino acids and aim to supplement a regular diet.

[Rationale for Exclusion Criteria]

1)–5) ensure the safety of the subjects, 6)–13) eliminate subjects who may interfere with the objectives of the study, and 13) ensures the safety of the personnel in charge of collecting and analyzing blood from subjects.

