**4.5 ENROLLMENT/ALLOCATION PROCEDURES**

### 4.5.1 Enrollment

The principal investigator/subinvestigator will select and enroll subjects according to the following procedures.

1) The details of the study will be explained to the prospective participants who meet all of the inclusion criteria described in 1)–4) and do not meet any of the exclusion criteria described in 1)–13) and who provide written informed consent to participate in the study.

2) Subject candidates will be selected according to the results of the screening tests.

3) Subjects will be selected from subject candidates according to the results of the pre-administration tests.

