**5.3 STUDY COMPLETION, SUBJECT DISCONTINUATION, AND WITHDRAWAL**

### 5.3.1 Study Completion

Each treatment phase will be considered complete after blood sampling and testing at the end of 48 h after study drug administration.

The study will conclude after completion of the 3 treatment phases.

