### 5.3.2 Subject Discontinuation or Withdrawal

The investigator may terminate or withdraw a subject from the study in case of the following:

1) If the subject requests withdrawal or declines participation

2) If the subject experiences an AE that undermines continuation of the study in the opinion of the principal investigator

3) If the subject is unable to take the study drug

4) If the subject is judged as ineligible to continue the study by the principal investigator

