### 5.3.4 Subject Replacement

Subjects will be replaced if discontinuation or withdrawal results in a sample size that falls below the required size for the study (15 subjects). The number of withdrawn subjects will be replaced, and the subjects will undergo test procedures beginning from phase I according to their allocated group. Samples collected from participants until discontinuation may be used for analysis as long as consent is obtained from the withdrawn subjects.

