**8. CRITERIA FOR EVALUATION AND ANALYSIS**

**8.1 TARGET POPULATION**

**8.1.1 Target Population for Pharmacokinetic Analysis**

Registered subjects who satisfy the inclusion criteria and do not meet the exclusion criteria as well as those who have completed sampling for pharmacokinetic analysis after administration of the study drug

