**9.1.5 Severity of Adverse Events**

1) Mild:

The event is generally temporary; it does not impair the person’s ability to conduct normal life functions (i.e., normal activities are possible) and does not require treatment.

2) Moderate

The event interferes with the person’s ability to conduct normal life functions (i.e., normal activities are accompanied by discomfort) and requires treatment.

3) Severe

The event severely impairs the person’s ability to conduct normal life functions (i.e., normal activities are onerous) and requires treatment.

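### Exclusion criterion 10 depends on drug use after dosing, so it cannot be settled at enrolment, and through 8.1.1 it can remove a dosed subject from the PK population for all three phases

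*Protocol*

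**What the plan says.** Criterion 10 in Protocol 4.4, repeated in the synopsis (1.4.4), reads "10) Subjects who used other agents from 7 days prior to study drug administration until completion of each treatment phase of the study". Section 5.3.1 fixes where that window closes: "Each treatment phase will be considered complete after blood sampling and testing at the end of 48 h after study drug administration".

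The neighbouring criteria are built differently. Criterion 8 covers the same window but asks about ability: "8) Subjects who are not able to stop taking medications (e.g., general cold, anti-allergy, anti-fungal, and Kampo medications) from 7 days prior". Criterion 7 (smoking and drinking) takes the same form, and criterion 9 (supplements) stops at dosing. Section 5.3.5 restates the medication ban as an instruction to subjects. It gives no consequence for a breach and no exception for treating an adverse event (AE).

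Section 4.5.1 applies the whole list at entry, to people who "do not meet any of the exclusion criteria described in 1)–13) and who provide written informed consent to participate in the study". Tables 2 and 3 place allocation on the day before the first dose.

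Section 8.1.1 builds the PK population from "Registered subjects who satisfy the inclusion criteria and do not meet the exclusion criteria", with a further clause on completed sampling. The safety population in 8.1.2 is everyone who took study drug.

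Section 5.3.2 opens with "The investigator may terminate or withdraw a subject from the study in case of the following" and lists four grounds. Item 2 is an AE that, in the principal investigator's opinion, stands in the way of continuing. Item 4 is the principal investigator's judgement that the subject is no longer eligible. Use of another drug is not named. Section 5.3.4 says "Subjects will be replaced if discontinuation or withdrawal results in a sample size that falls below the required size", that size being 15. Section 4.2 sets the target at 21. Section 9.1.5 describes a moderate AE as one where "normal activities are accompanied by discomfort) and requires treatment", and 9.2 has any treatment of an AE recorded in the CRF.

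**The concern.** An eligibility criterion should be answerable before allocation. Criterion 10 turns on what the subject actually takes, and much of its window lies after randomisation and dosing. Since 8.1.1 refers back to the exclusion criteria, an event during treatment can decide who is in the PK population.

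Three things are at stake. First, membership of the PK population may depend on what happened after a dose, in a crossover meant to describe PK at three doses. Second, 8.1.1 is written by subject, so a breach confined to one phase also costs the two phases it did not touch. Third, the replacement rule watches a different count from the one the PK analysis uses.

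**Working it through.** **1. How much of the window is known at allocation.** Each phase's window runs from 7 days before dosing (4.4) to 48 h after (5.3.1): 7 + 2 = 9 days. Three phases give 3 × 9 = 27 days. Allocation is on Day -1 of phase I (Tables 2 and 3), when about 6 of those days have passed. About 27 − 6 = 21 of 27 days (78%) lie after allocation, so criterion 10 cannot be cleared at the point where 4.5.1 applies it.

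**2. Whether this is the document's usual form.** Of the four criteria on consumption (7 to 10), 7 and 8 have post-dose windows but ask about ability to stop, which can be judged at entry. Criterion 9 concerns actual use but ends at dosing. Only criterion 10 combines actual use with a post-dose window. Criterion 8 and 5.3.5 already cover medication over the same period.

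**3. Cost of one breach under the literal text.** Planned profiles: 21 subjects × 3 phases = 63. One subject removed: 3/63 = 4.8%. At least two of the three profiles come from phases without a breach if only one phase was affected. If the breach is in phase I and the subject continues, PK sampling in the other two phases takes 2 × (13 × 12 mL) = 312 mL for profiles that the literal 8.1.1 does not admit. That blood is already within the planned total of 8 + 3 × (16 + 156) = 524 mL, which matches 7.1.5; it is not additional.

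**4. The two counts.** Section 5.3.4 triggers on the number left after discontinuation or withdrawal. Section 8.1.1 counts those who do not meet the exclusion criteria. If 15 subjects remain and 2 of them have breached criterion 10 without being withdrawn, 5.3.4 sees 15 and requires nothing, while 8.1.1 admits 15 − 2 = 13. To reach that point, 21 − 15 = 6 subjects (6/21 = 28.6%) must already have been lost. The case shows what the rule can miss; it is not a forecast.

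**5. How likely a shortfall is.** The protocol gives no rate of drug use, so the rates below are assumptions. Let q be the chance that a subject takes another drug inside the window in one phase, independent across phases and subjects, with no other losses. A subject breaches at least once with probability P = 1 − (1 − q)³. Seven or more breaches among 21 leave at most 14 PK-eligible subjects.

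| q per phase (assumed) | P | Expected breaches, 21 × P | Chance of 7 or more |
|---|---|---|---|
| 2% | 5.9% | 1.2 | 0.01% |
| 5% | 14.3% | 3.0 | 2.2% |
| 10% | 27.1% | 5.7 | 33% |

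At low rates the margin of six absorbs the loss. The shortfall becomes material only if breaches are common or add to other withdrawals.

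**The case against.** The strongest reply is that 8.1.1 speaks of registered subjects and 4.5.1 checks the criteria at entry, so 8.1.1 may mean eligibility at entry only. Its clause on completed sampling is also ambiguous. Section 8.2.3 leaves fixing the analysis sets to an SOP, and PK methods go to a separate plan that is not at hand. Pre-dose tests are repeated before phases II and III, which gives the investigator a checkpoint, and a window tied to each phase could be meant as a phase-by-phase condition. These points show that a milder intention is possible. They do not remove the conflict: the entry-only reading contradicts criterion 10's own window, and nothing in this protocol states a different population rule or a phase-level one.

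A reader might infer that the protocol neither stops nor replaces such a subject. The text does not support that. Items 2 and 4 of 5.3.2 let the investigator withdraw the subject, who then counts under 5.3.4. Stopping is discretionary and replacement conditional; neither is absent.

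A reader might also infer that every moderate or severe AE leads to exclusion. Section 9.1.5 speaks of treatment, which need not be a drug, and only use inside the window counts.

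Finally, a reader might infer that high-dose reactors drop out of the PK results. Section 6.3 reports no AEs associated with TJ-43 after a single 7.5 g dose in the preliminary study. The safety population is unaffected, so such events are not lost to the safety evaluation.

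**Conclusion.** The point holds as a drafting fault with a real route into the analysis. Criterion 10 cannot be decided when 4.5.1 requires. Followed literally through 8.1.1, one post-dose breach removes a dosed subject's three profiles (4.8% of the planned total) because of a post-randomisation event. A subject who is kept in the study still counts toward 15 without being PK-eligible.

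The size is likely small. With a margin of six, falling below 15 through breaches alone is improbable at an assumed 2% or 5% per phase and sizeable only near 10%, and the protocol gives no rate with which to choose between them. Selection related to dose is possible in principle but not shown. The conclusion rests on reading 8.1.1 as written and on the absence of any other population rule in this document. The change is worth making because it costs little, not because a large bias is expected.

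**What to change.** - **1.4.4 and 4.4:** limit criterion 10 to use of other agents that can be established before allocation. Leave later use to the conduct rule already in 5.3.5.
- **8.1.1:** define PK evaluability by subject and phase. Record a later breach as a deviation of the phase concerned, decide that phase's evaluability before its concentrations are seen, and retain unaffected phases.
- **5.3.4:** count PK-evaluable subjects against the required 15, and state how many evaluable phases a subject needs to be counted.
- **Reconcile** 4.4, 5.3.2, 5.3.4, 5.3.5 and 8.1.1 so that they treat the same event alike. Which drugs are allowed, and when a subject should stop, is a clinical matter on which this point takes no position.

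The cost is protocol wording, with no added visits, tests or blood at the planned sample size. The downside is a documented evaluability decision for each affected phase and, if breaches prove common, possibly an earlier replacement than the current count would trigger.
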